Out of 319 infants, 47 (14.7%) were colonized with an MRGN pathogen, of which 30 infants (9.3%) tested positive for a 2MRGN pathogen. One infant was colonized with 2MRGN *E. coli* at birth, 15 infants were colonized within the first 5 weeks of life (figure 1). The 2MRGN pathogens were isolated from pharyngeal swabs (n=12), rectal swabs or fecal samples (n=19) or conjunctiva (n=1). Four infants were colonized with > 1 MDRO including two infants with MRSA and 3MRGN *E.coli* and two infants with 2MRGN *Enterobacter cloacae* and either 2MRGN *E.coli* or 2MRGN *Klebsiella pneumoniae*. Colonization with 2MRGN occurred at a median of 33 days. Figure 1 describes the timepoint of first colonization with MDRO in vulnerable infants. Seven infants were initially colonized with antibiotic susceptible bacteria and acquired 2MRGN features during hospital stay.

Out of 319 of infants, 296 received antibiotic therapy for a median duration of 7 days, 252 infants were already started on antibiotics on day 1 of life. MDRO colonized infants were treated for a median of 7 days. Among 2MRGN colonized infants, one infant developed a 2MRGN *E.coli* sepsis on day 6 of life, two infants were diagnosed with 2MRGN sepsis (*Enterobacter* spp.) between day 7 and 28 of life and five infants were treated for culture-negative sepsis. Our data are in line with previous single center studies in Germany with evidence of MDRO colonizing infants in 4.9% of 635 neonates, 12.7% of 584 screened neonates and 15.3% of 1407 preterm infants, respectively (20-22). In a recent multicenter RCT on the effect of probiotics to prevent MDRO colonization in preterm infants 28-32 weeks of gestation, we confirmed center-specific MDRO colonizing rates between 5-20% (23). In the BALTIC trial, we therefore estimated the number of 2MRGN colonized infants to be 10% during the hospital stay.

[figure not shown]

**Figure 1:** First detection of MRGN, MRSA, MRSA or Vancomycin resistant enterococci (VRE)

MRDO = Multi-drug resistant organisms; KRINKO = German Commission on Hospital Hygiene and Infection Prevention, MRGN = Multidrug-resistant Gram negative bacteria, 2MRGN (resistant to Piperacillin and Cefotaxim or Ceftazidim), 3MRGN (resistant to Piperacillin and Cefotaxim or Ceftazidim and fluorquinolones), MRSA = methicillin-resistant *Staphylococcus aureus*, VRE = Vancomycin resistant *Enterococci*

Additional first detections after the 15th week of life: n = 4 2MRGN pathogens

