### *Outcomes*

The primary endpoint is the rate of HA bloodstream infections with Gram-negative pathogens in all preterm and newborn infants who received colonization screening. This outcome is defined clinically according to NEO-KISS criteria (at least two clinical signs of sepsis + one laboratory sign, e.g. increase in C-reactive protein > 10mg/l) after 72 hours of life and requires the detection of a Gram-negative pathogen in the blood culture. Blood-culture isolates will be sent from the study centers to the study management.

Key secondary endpoint is the 2MRGN transmission rate which is assumed if another infant is colonized with the same 2MRGN pathogen after 2MRGN colonization or infection of an infant

requiring intensive care in a temporal (maximum 90 days) and spatial context (potential contact in the intensive care unit) (26). This assumption is made if, in addition to pathogen identification, the antimicrobial susceptibility testing patterns are identical. Suspected transmission of or bloodstream infection with an 2MRGN pathogen will be reported to the study management as severe adverse event within 24 hours.

Transmission/outbreak management remains the responsibility of the local interdisciplinary infection control team and is carried out according to local standards, including the decision whether to initiate genetic identity testing in the acute situation. 2MRGN isolates will be shipped from local sites and molecular typing will be performed at the Department of Infectious Diseases and Medical Microbiology at the University of Lübeck. Other secondary outcomes at the level of study sites per period ("study phase") are:

- Rate of clinical and culture proven infections
- Rate of infection outbreaks
- Number of initiated antibiotic cycles
- Duration of antibiotic treatment (days)
- Exposure to reserve antibiotics, including Carbapenems per study site in % infants.

To assure documentation of relevant outcomes, intensive interdisciplinary collaboration (neonatology/infectiology/hygiene/pharmacy/management) is required. Data are collected by monthly cluster report forms on infection and transmission rates and yearly surveillance of antibiotic use, disinfectant consumption, and cost estimations.

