## 5 Database

The database is the data taken over from the clinical project management team according to Chapter 3. In this, data is documented entirely on an aggregated level, i.e., per month per site.

The data is structured as follows:

- Every of the 12 sites participates in the study in two phases, in one of which hand disinfection alone (IV), in the other hand disinfection plus gloves and gowns is applied (CO). The order of the two phases is randomized.
- Every phase has a duration of 12 months, so that for every site, data is collected for 24 months.
- Each of the two phases at one site is considered one cluster.
- Given the aggregation of the data in months, the observational unit is the month (month-level variables).
- Some variables give the count of patients with a specific event. From this and the number of admissions in that month, the number of patients without the specific events is constructed as well as data on patient-level is constructed for analyses (patient-level variables).

To obtain the count of patients without a specific event, the number of events is subtracted from the number of admissions [Aufnahmen\_Neo] rendering the following additional variables:

| Count of patients with the event
(original variable) | Count of patients without the event
(constructed variable) |
|---------------------------------------------------------|---------------------------------------------------------------|
| Anzahl_gramNeg_nurLOS                                   | Anzahl_gramNeg_nurLOS_negativ                                 |
| Transm_Patient                                          | Transm_Patient_negativ                                        |
| Transmission_2MRGN_Patient_SAE                          | Transmission_2MRGN_Patient_SAE_negativ                        |
| Anzahl_kl_Sepsis_allg                                   | Anzahl_kl_Sepsis_allg_negativ                                 |
| Anzahl_BKpos_Sepsis_allg                                | Anzahl_BKpos_Sepsis_allg_negativ                              |
| Anzahl_2MRGN_LOS                                        | Anzahl_2MRGN_LOS_negativ                                      |

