| Sensitivity analyses: Confounding         | 
As further sensitivity analyses, the same models are estimated as above with simultaneously taking possible confounders into account:
 <pre>geeglm(cbind(Anzahl_gramNeg_nurLOS, Anzahl_gramNeg_nurLOS_negativ) ~ Randomisierung + Confounder, family = binomial(link = "identity"), id = Cluster, corstr = "independence")</pre> 
with the variable <code>Randomisierung</code> indicating the phase (CO vs. IV) and <code>Confounder</code> being one of the three variables
 
 
• Percentage of shifts with understaffing in the month [<code>GBA_Prozent</code>]
 
• Count of days with blocked beds in the month [<code>Tage_Bettensperrung</code>]
 
• additional workload in the NICU by patients > 28 days of age [<code>Aufnahme_Päd</code>].
 
 
The risk difference with regard to the intervention is estimated accordingly with 95% confidence intervals.
 |
| Hypothesis                                       | n.a.                                                                                                                                                                                                                                                                                                                                                                                                                                                                                                                                                                                                                                                                                                                                                                                                                                                                                                                                                |

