### 9.4.2 Efficacy Outcome Variables on the level of patients

For the following binary variables, the count of patients without the event is reconstructed:

- Transmission of 2MRGN [Anzahl\_gramNeg\_nurLOS\_negativ]
- Any transmission [Transm\_Patient\_negativ]
- Any BSI [Anzahl\_BKpos\_Sepsis\_allg\_negativ]
- 2MRGN BSI [Transmission\_2MRGN\_Patient\_SAE\_negativ]
- Clinical infection [Anzahl\_kl\_Sepsis\_allg\_negativ]

For these, the below analyses are performed:

|                  |                                                                                                                                                                                                                                                                                        |
|------------------|----------------------------------------------------------------------------------------------------------------------------------------------------------------------------------------------------------------------------------------------------------------------------------------|
| Outcome variable | Anzahl_gramNeg_nurLOS, Anzahl_gramNeg_nurLOS_negativ, Transm_Patient, Transm_Patient_negativ, Anzahl_BKpos_Sepsis_allg, Anzahl_BKpos_Sepsis_allg_negativ, Transmission_2MRGN_Patient_SAE, Transmission_2MRGN_Patient_SAE_negativ, Anzahl_kl_Sepsis_allg, Anzahl_kl_Sepsis_allg_negativ |
| Endpoint         | Transmission of 2MRGN, any transmission, any BSI, 2MRGN BSI, clinical infection                                                                                                                                                                                                        |
| Effect measure   | Risk difference                                                                                                                                                                                                                                                                        |

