| Adjustments for covariates | None                                                                                                                                                                                                                                                                                                                                                                                                                                                                                                                                                                                                                                                                                                                                                                                                                                                                                                                                                                                                                                                                                                                               |
| Main estimator             | 
Risk differences are estimated from a GEE logistic regression model with identity link using the following command from the R-library <code>geepack</code>:
 <pre>geeglm(cbind(events, nonevents) ~ Randomisierung, family = binomial(link = "identity"), id = Cluster, corstr = "independence")</pre> 
with the variable <code>Randomisierung</code> indicating the phase (CO vs. IV) and <code>events</code> and <code>nonevents</code> being one of the five variable pairs
 
 
• <code>Anzahl_gramNeg_nurLOS</code>, <code>Anzahl_gramNeg_nurLOS_negativ</code>
 
• <code>Transm_Patient</code>, <code>Transm_Patient_negativ</code>
 
• <code>Anzahl_BKpos_Sepsis_allg</code>, <code>Anzahl_BKpos_Sepsis_allg_negativ</code>
 
• <code>Transmission_2MRGN_Patient_SAE</code>, <code>Transmission_2MRGN_Patient_SAE_negativ</code>
 
• <code>Anzahl_kl_Sepsis_allg</code>, <code>Anzahl_kl_Sepsis_allg_negativ</code>
 
 
The risk difference with regard to the intervention is estimated accordingly with 95% confidence intervals.
 |

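### The key secondary endpoint, 2MRGN transmission, is analysed without the number of 2MRGN source infants, which costs precision but does not bias the comparison

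*Combined protocol and SAP*

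**What the plan says.** The Outcomes section of the protocol defines the endpoint by reference to an earlier 2MRGN-positive infant, within at most 90 days and with possible contact in the unit: "Key secondary endpoint is the 2MRGN transmission rate which is assumed if another infant is colonized with the same 2MRGN pathogen after 2MRGN colonization". It names no denominator. According to the Trial design section, the regimens differ only in the measures used for infants with a 2MRGN-positive screen.

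The SAP supplies the denominator. In section 5, "the number of events is subtracted from the number of admissions", which yields the complement "Transmission_2MRGN_Patient_SAE_negativ". Section 9.4.2 lists the patient-level endpoints ("Transmission of 2MRGN, any transmission, any BSI, 2MRGN BSI, clinical infection") and states "Risk differences are estimated from a GEE logistic regression model with identity link", with "Adjustments for covariates | None". Section 9.4.1 adds a yes/no version per month, also without covariates.

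No count of 2MRGN-positive infants appears as denominator, offset or covariate. The three confounder models in SAP 9.3 concern the primary endpoint and use understaffing, bed closures ("Count of days with blocked beds in the month") and workload from older infants. SAP 5.2 records a monthly percentage of 2MRGN patients not treated as randomised, but the SAP names no variable for the count behind it. All secondary analyses are descriptive.

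**The concern.** No transmission can occur without a source. Barrier care for known carriers acts on this endpoint mainly through how many secondary cases each source produces. The planned measure multiplies that quantity by the number of sources, which varies by chance between the two phases of a site. A single-site illustration: 20 index infants with 4 secondary cases and 10 index infants with 2 give 4/150 = 2.7% and 2/150 = 1.3% of admissions, although both are 0.20 per index infant.

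The trial asks whether dropping gloves and gowns does harm, and the protocol calls transmission the key secondary endpoint. Readers will look at its estimate and interval even though no test is attached. An interval wider than necessary makes it harder to see an increase in transmission or to rule one out.

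**Working it through.** **Inputs from the documents.** 150 admissions per site and year, 12 sites and 10% colonised (protocol, Sample size calculation and statistical analysis). Check of the plan's own figure: 12 × 150 × 0.10 = 180 colonised infants per 12 months, as stated, or 15 per site and phase. For the spread between centres, the Benchmarking section reports "we confirmed center-specific MDRO colonizing rates between 5-20" per cent.

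**Inputs assumed, because the documents do not give them.** Secondary cases per index infant, r, from 0.1 to 0.5. Extra phase-to-phase variation in source numbers within a site, c (coefficient of variation), from 0 to 0.5.

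**Scale.** A per-admission risk difference and a per-index rate have different units, so precision is compared on the log rate ratio. With equal admissions, the per-admission log rate ratio is the log ratio of event counts.

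**Formula.** The 180 colonised infants per regimen comprise N index infants and N × r secondary cases, so N = 180/(1 + r). For one regimen, with equal sites:

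- per index infant: variance ≈ 1/(N r)
- per admission: variance ≈ 1/(N r) + 1/N + c²/12

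The ratio is 1 + r + N r c²/12, and the saving is 1 − 1/ratio. For r = 0.5 and c = 0.5: N = 180/1.5 = 120, ratio = 1.5 + 120 × 0.5 × 0.25/12 = 2.75, saving 64%.

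| r | N | c = 0: ratio, saving | c = 0.3: ratio, saving | c = 0.5: ratio, saving |
|---|---|---|---|---|
| 0.1 | 164 | 1.10, 9% | 1.22, 18% | 1.44, 31% |
| 0.3 | 138 | 1.30, 23% | 1.61, 38% | 2.17, 54% |
| 0.5 | 120 | 1.50, 33% | 1.95, 49% | 2.75, 64% |

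**Simulation with no regimen effect** (20,000 trials per scenario, 12 sites, site multipliers 0.5 to 2 to reflect 5-20% around 10%). The saving is about 8-33% at c = 0 and up to about 66% at c = 0.5, in line with the table. For c = 0.3, the SD of the log rate ratio is 0.323 per admission against 0.268 per index infant at r = 0.2 (saving 31%), and 0.292 against 0.225 at r = 0.3 (saving about 40%).

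**In interval width.** The per-admission interval is √1.10 = 1.05 to √1.50 = 1.22 times as wide under Poisson variation alone, and about √(1/0.34) = 1.7 times at the 66% end.

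**Bias and error rate.** The mean risk difference is about 0 in every scenario. A cluster-robust 95% interval excludes 0 in about 2-7% of null trials, depending on the spread between sites.

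**Months without a source.** If first detections are Poisson, the probability of none in 90 days is exp(−150 × p × 90/365). At the plan's p = 10% this is exp(−3.70) = 2.5%. At p = 5% × 30/47 = 3.2% it is 31%. The second value is a low-prevalence extreme: it takes the lowest centre rate and applies one centre's share of 2MRGN among MRGN carriers to an MDRO rate.

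**The case against.** **Admissions are a legitimate denominator.** Admitted infants are the population at risk, the choice matches the primary analysis, and the per-admission risk captures the total effect of a regimen on a unit. This stands, and is why the planned analysis should remain.

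**This is noise, not bias.** This also stands. A reader might infer that unequal source numbers create a false regimen effect. The order of phases is randomised, the mean difference is about 0, and the robust interval keeps roughly its nominal error rate. Stable differences between centres largely cancel in the point estimate, though not in the interval, because SAP 9.3 treats the two phases of a site as independent.

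**The size rests on assumed inputs.** Correct. At r = 0.1 with Poisson variation the saving is under 10%.

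**The index count is itself post-randomisation.** This is the strongest objection. A reader might infer that index infants are all imported, so that adjusting for them cannot touch the regimen effect, or that differences per admission reflect importation only. The Benchmarking section does not support that. Of 30 2MRGN-positive infants, one was colonised at birth, colonisation occurred at a median of 33 days, and seven infants first carried susceptible bacteria. Most first detections are therefore acquired in hospital, some perhaps through an undetected carrier, and an offset could remove a little of a true effect. What limits this is that undetected carriers are cared for alike under both regimens. A first detection with no known match in the previous 90 days should be at most weakly affected.

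**The data may already exist.** The case report form is not among the documents, and the percentage in SAP 5.2 implies that sites count 2MRGN patients. That lowers the cost but does not put a source count into the analysis.

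**Conclusion.** The point holds as a loss of precision. SAP 9.4.1 and 9.4.2 leave out the number of 2MRGN source infants, although the endpoint requires a source and the regimens differ only in the care of known carriers. A per-index analysis would reduce the variance of the log rate ratio by about 8-33% under Poisson variation in sources, and by up to about 66% at an assumed coefficient of variation of 0.5, for an assumed 0.1 to 0.5 secondary cases per index infant.

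The documents do not support reading this as a biased contrast. Nor do they support the inference that a large share of months is source-free in general: at the plan's own 10% it is about 2.5%, and 31% is the low-prevalence extreme. The analysis is descriptive, so no formal conclusion of the trial depends on it. A supplementary analysis is worth adding because the endpoint is called key and the cost is low.

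**What to change.** 1. Record per site and month the number of 2MRGN index infants: first detection, with no matching 2MRGN-positive infant in the unit in the previous 90 days. This mirrors the window in the endpoint definition.
2. Report index infants by regimen.
3. Keep the per-admission risk difference in SAP 9.4.2 as the planned analysis.
4. Add to SAP 9.4.2 a supplementary log-link GEE of secondary cases per site and phase, with offset log(index infants per site and phase).
5. State in the SAP that the index count could be influenced slightly by the regimen, and that the per-index result is to be read beside the per-admission result and the index counts.
6. Reconcile the variable names first. The list in SAP 9.4.2 gives 2MRGN transmission the complement of the gram-negative infection count and gives 2MRGN BSI "Transmission_2MRGN_Patient_SAE_negativ", whereas the tables in SAP 5 assign the latter to 2MRGN transmission.

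The cost is one extra count per site and month and one extra model. Sites must already identify each 2MRGN-positive infant to apply the regimen. The protocol (Outcomes, Data management) also has 2MRGN isolates shipped centrally and stored with collection date and cluster, so the counts may be recoverable later. Carriers missed by screening will lead to some infants being wrongly classed as index cases.

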### *Stopping rules*

The coordinating investigator has the right to discontinue the study in centers that experience insufficient study conduction, technical-logistic problems and repetitive outbreak situations that require extended barrier precautions in all patients, which would interfere with the study

questions. The study sites will be instructed to discontinue the study only if substantial problems occur. The coordinating investigator will be informed immediately, should ethical or safety concerns occur at any study site.

#### *Quality assurance and monitoring*

During the study, quality assurance measures including supervision by authorities will be implemented. All study centers have agreed that a study monitor will review the data collection before, during and after the study to ensure that the study is conducted in accordance with the protocol, with SOPs and the corresponding regulations of GCP. In addition to the monitoring procedures, audits will be carried out in accordance with the ICH-GCP Guidelines. In the context of an audit, the planning, execution, and analysis of the study are checked to evaluate whether all study processes are conducted in accordance with the German law or the ICH Guidelines. This includes the storage of data and the organisation of the study centres, the original documents in accordance with data management agreements between sponsors and participating centres. The objective of audit measures is to ensure that all results and conclusions that ultimately appear in the final report are readable from the raw data.

